## Methods

### Conceptual Model

The conceptual model that guided our development and testing of a digital social media intervention in patients with depression or anxiety is shown in Figure 1.

It is grounded in the principles of MBC. We have an expansive view of MBC, which posits that systematically monitoring multiple sources of collateral information, in addition to patient- and clinician-rated outcomes measures, throughout the course of treatment can significantly improve clinical outcomes. In this case, the intervention is designed to gather collateral information about the patient’s digital social activity, which growing evidence suggests can provide important real-time insights into the patient’s mental health status. We hypothesize that such an intervention may improve downstream clinical outcomes through 2 mediating pathways. In the first pathway, routinely gathering collateral information on the patient’s digital social activity may lead to better detection of clinically actionable targets. Clinically actionable targets may include the early detection of signals that the patient’s course of illness is starting to worsen or of interpersonal struggles that may precipitate declines in the course of illness. Earlier detection of these clinically actionable targets can lead to more rapid treatment adjustments to address emerging issues before they become more intractable problems. The treatment adjustments may involve a wide variety of interventions, including changes in medication; frequency and duration of clinical visits; the focus of psychotherapy; and outreach to parents, the school, or other responsible parties in the patient’s social support network. In the second pathway, the digital social media intervention may improve the therapeutic alliance by fostering more informed and open communication between the patient and clinician, and a substantial body of evidence indicates that a strong therapeutic alliance is crucial to the success of psychiatric treatment [39]. The conceptual model hypothesizes that through these 2 mediating pathways, the intervention may improve more proximal clinical outcomes on clinical symptomatology, which, in turn, leads to improvements in more distal outcomes, such as overall functioning. It is possible that routinely collecting information about the patient’s digital social activity may lead to the false positive detection of clinically actionable targets, leading to unnecessary and perhaps harmful changes in treatment. Another possibility is that data collection may disrupt the therapeutic alliance between the patient and clinician by raising concerns over privacy and engendering distrust, which together could ultimately lead to worse clinical outcomes. These are empirical questions about the impact of the proposed intervention that need to be tested and are the focus of our randomized pragmatic trial.

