#### Study Procedures

All patient participants downloaded the Bark app and went through the process of connecting their social media and electronic communication platforms to the app. To promote trust and participation in the study, we allowed patients to decide which platforms to connect to the Bark app. While patients retained final control of the decision, we explained to them that their most frequently used apps would provide the most relevant information. Patients were randomized within strata formed by treating clinicians in a 1:1 ratio with blocks of size 2 to either the dashboard intervention or TAU. The purpose of stratified randomization in blocks was to promote balance in the number of patient participants in the 2 treatment arms seen by each clinician, thereby reducing the impact of differences between treating clinicians on comparisons of patient outcomes between the 2 arms. For patients in the intervention arm, the electronic dashboard was delivered to the treating clinician before scheduled clinical visits. The clinician and patient collaboratively decided when and how to use the dashboard in the session during each clinical encounter. For patients in the TAU arm, the clinician did not receive a clinical dashboard for review. After the initial visit to download the Bark app, there were no more study-specific research visits. To be pragmatic and stay as close to the real-world setting as possible, patients continued to be seen by their clinician as clinically indicated. The first regularly scheduled clinic visit with their clinician after the patient consented and downloaded the Bark app was considered the study’s baseline visit. Patients were then followed through their clinical care for up to 6 months, and all study measures were completed during their regularly scheduled clinic visits.

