#### Statistical Analysis

The primary outcome of the trial is the difference in depressive symptoms measured by the PHQ-9 total score over the course of follow-up between the dashboard intervention and TAU arms. Secondary outcomes include differences in anxiety symptoms measured by the GAD-7 total score and in the more distal outcome of functioning, as measured by the SF-36 MHC. Because the PHQ-9 and GAD-7 were collected at each clinic visit and the SF-36 MHC at baseline and end of the study, there are repeated measures over time for each scale within individual patients. We plan to use random effects linear regression models to test for differences in scores on these measures between the 2 treatment arms. We will include fixed effects terms for the treatment arm as well as for time. Furthermore, we will consider including fixed effects terms for potential confounders, such as demographics (eg, age, sex, and race), and clinical factors, such as primary diagnosis and the number of clinic visits as an indicator of clinical severity. We will also include random effects for individuals to account for the correlation in outcome measures within repeated measures of the same individual as well as for clinicians, if indicated, to account for the potential clustering effects of treatment within clinicians. The primary statistical test of interest will focus on the fixed effects term for treatment, which will provide an estimate of the mean differences in the outcome measures between the 2 treatment arms, controlling for time. We will consider different functional forms of the time covariate and use the one that provides the best fit to the data on changes in score over time. Given that patients will be enrolled in the study regardless of their current mental health status and scores on these outcome measures, we consider the model in which we control for time to be the most appropriate test of differences between the treatment arms. However, we may consider examining interactions between treatment and time to see whether changes in the scores over time differ between the 2 treatment arms. We will use the conventional threshold of *P*<.05 to declare differences statistically significant.

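### The number of clinic visits is offered as a confounder for the outcome models, although it appears to be a post-randomisation count that the conceptual model lists among the dashboard's possible routes of effect

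*Protocol article*

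**What the plan says.** Under Statistical Analysis, the primary comparison is the treatment term in a random effects linear model of PHQ-9 with fixed effects for arm and time. The text then adds that "we will consider including fixed effects terms for potential confounders", giving demographics and "clinical factors, such as primary diagnosis and the number of clinic visits as an indicator of clinical severity" as examples. The same approach serves GAD-7 and SF-36 MHC. It is reused for the WAI-SR and, in logistic form, for the M-CICAS.

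Study Procedures describes how visits come about. After the app is set up there are no further research visits; "patients continued to be seen by their clinician as clinically indicated". "Patients were then followed through their clinical care for up to 6 months". In the intervention arm, "the electronic dashboard was delivered to the treating clinician before scheduled clinical visits"; in the TAU arm the clinician receives none.

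The Conceptual Model describes treatment adjustments that may follow earlier detection of problems as "including changes in medication; frequency and duration of clinical visits; the focus of psychotherapy", among others.

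**The concern.** Allocation was randomised "in a 1:1 ratio with blocks of size 2 to either the dashboard intervention or TAU", so severity at entry cannot differ systematically between arms, and no covariate is needed to remove confounding of the arm comparison. A baseline severity covariate can add precision. A variable generated during follow-up is a different matter.

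A follow-up visit count has three properties that make it unsuitable:

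- It accrues after allocation, and the clinician who influences it knows the arm.
- On the article's own rationale it reflects how ill the patient is, and that is what the PHQ-9 measures. It is therefore partly a consequence of the outcome.
- It belongs to a class of treatment change through which the intervention is hypothesised to work.

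Comparing arms at equal visit counts then no longer compares the randomised groups. The error can go either way. If the dashboard prompts extra visits without improving symptoms, a dashboard patient with a given count is on average less ill than a TAU patient with the same count, and the dashboard looks beneficial. If the dashboard helps through extra visits, or helps and also reduces visits, part or all of the benefit is adjusted away.

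**Working it through.** **1. Which count is meant.** The Statistical Analysis section gives no window. Study Procedures makes the number of follow-up visits variable, PHQ-9 is recorded at each of them, and Table 1 lists no visit count at baseline. These point to the follow-up count without proving it.

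**2. The plan's own figure, to fix the scale.** Sample Size states 80% power for d = 0.5 with 100 patients and at least 3 measures. With 50 per arm, two-sided 5% (sidedness assumed) and within-patient correlation ρ (not stated), the SD of a 3-measure mean is √((1 + 2ρ)/3). At ρ = 0.7 this is √0.8 = 0.894; then 0.5/(0.894 × √(2/50)) = 2.80, and 2.80 − 1.96 = 0.84, a power of 79.8%. A single measure gives 69.7% (t test). The 80% is reproducible under a plausible correlation, and the present point does not depend on it.

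**3. Why adjustment moves the estimate.** In least squares with arm and visit count:

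adjusted estimate = unadjusted estimate − b × Δ

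Here b is the within-arm slope of PHQ-9 on visit count and Δ is the difference between arms in mean visits. Bias needs both to be non-zero. If sicker patients are seen more, b > 0; if visits help and severity does not drive them, b < 0.

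**4. Size under assumed inputs.** 4,000 simulated trials per case, 50 per arm, outcome the patient-mean PHQ-9 in SD units, ordinary least squares. None of the following is in the documents. Visits are 1 + Poisson with mean about 8, so about 9 in TAU. In all but the third group of rows (benefit through visits), latent severity raises the log visit rate by 0.3 per SD. Severity raises PHQ-9 by 0.7 SD per SD. In the third group severity does not drive visits and each visit lowers PHQ-9 by 0.15 SD.

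| Case | Visit rate × | Δ visits | Unadjusted estimate (rejected) | Adjusted estimate (rejected) |
|---|---|---|---|---|
| No effect, visits unchanged | 1.00 | 0.0 | 0.00 (4.8%) | 0.00 (4.8%) |
| Effect −0.5, visits unchanged | 1.00 | 0.0 | −0.50 (70%) | −0.50 (79%) |
| No effect, more visits | 1.11 | 0.9 | 0.00 (4.9%) | −0.10 (8.6%) |
| | 1.22 | 1.8 | −0.01 (4.4%) | −0.21 (21%) |
| | 1.35 | 2.9 | 0.00 (4.7%) | −0.32 (39%) |
| Benefit wholly through visits | 1.22 | 1.8 | −0.27 (21%) | 0.00 (4.3%) |
| | 1.35 | 2.8 | −0.42 (47%) | 0.00 (5.1%) |
| | 1.65 | 5.2 | −0.79 (95%) | 0.00 (4.8%) |
| Effect −0.5, fewer visits | 0.82 | −1.5 | −0.50 (69%) | −0.31 (39%) |
| | 0.74 | −2.2 | −0.50 (70%) | −0.23 (22%) |
| | 0.61 | −3.3 | −0.50 (69%) | −0.09 (7%) |

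The formula in step 3 accounts for these. In the 1.22 null case the shift of −0.20 over 1.83 visits implies b of about 0.11 SD per visit; in the 0.82 case, 0.185/1.52 gives about 0.12.

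**5. Sensitivity to the model.** A second simulation, with weekly PHQ-9, visit probability depending on the current score and a random-intercept model, gave 24% false positives when mean visits rose from 7.7 to 8.7 (13%) and 57% when they rose to 9.5 (23%). The direction agrees, but the rates are between two and three times those above for similar rises. Only the direction is robust.

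**The case against.** The strongest reply is that the article does not commit to this adjustment. The terms it says it will include are arm and time; visit count is an example in a list to be considered, and the model controlling for time is called the most appropriate test. A reader might infer that the primary analysis is going to be adjusted for visits; the text does not say so. This stands, and it limits the severity. It does not remove the point, because the article names a specific variable as a confounder, gives a rationale that fails for a follow-up count, and leaves open a choice that can change the primary result.

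Second, patients were already in ongoing care, so a count of visits before randomisation is possible and would be a legitimate severity marker. A reader might take it as settled that the count accrues after allocation; that is an inference, though the better-supported one.

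Third, the Conceptual Model says only that treatment adjustments may include visit frequency. It does not establish that the dashboard changes visits, and the documents give no figure. If visits are unaffected, adjustment does no harm and, in the simulation, raises power from 70% to 79%. That too stands. However, the plan cannot rely on visits being unaffected while hypothesising that they may change, and a pre-randomisation severity covariate is a safe way to seek precision.

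**Conclusion.** Wrong as written, and it should be fixed. If counted during follow-up, the number of visits is not a confounder of a randomised comparison and does not belong in the outcome models. The conclusion rests on two readings: that the count is a follow-up count (inferred), and that the dashboard may alter visit frequency (hypothesised in the article, not shown). Where both hold, the bias can create an effect, with false positives of about 9% to 39% for a visit rate 11% to 35% higher, and can shrink or erase a real one. These sizes illustrate assumed inputs and are not predictions for this trial. The documents do not support saying that the primary result will be biased, only that the plan admits a variable that can bias it and leaves the decision open.

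**What to change.** - Exclude the follow-up visit count from the primary and secondary outcome models, and from the exploratory WAI-SR and M-CICAS models that reuse the approach.
- Fix the covariate list in advance and restrict it to variables measured before randomisation. For severity, use a PHQ-9 completed before allocation. The article defines the baseline visit as the first regular visit after consent and app download, without saying whether randomisation came before or after it, so the timing must be confirmed. A visit count in a fixed window before consent is an alternative if it can be obtained; Data Management mentions only PHQ-9 and GAD-7 as coming through the health record.
- Report the follow-up visit count by arm, descriptively or in an exploratory mediation analysis.

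The cost is one line of analysis wording. No new data are needed unless the pre-consent count is wanted. The article states that data collection is complete and results are to be reported separately, so the change should be recorded before the arm comparison is run or, if it has been run, disclosed with it.

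### Randomisation is stratified by treating clinician, but the clinician term is optional in the primary model; it should always be included (minor, free improvement)

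*Protocol article*

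**What the plan says.** Study Procedures (Protocol article) fixes the design: "Patients were randomized within strata formed by treating clinicians in a 1:1 ratio with blocks of size 2". It gives the purpose as "reducing the impact of differences between treating clinicians on comparisons of patient outcomes between the 2 arms".

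Statistical Analysis sets out the model for the PHQ-9, GAD-7 and SF-36 MHC. Some terms are definite: "We will include fixed effects terms for the treatment arm as well as for time", together with a random effect for each patient. Clinician is not definite. A random effect is promised for patients "as well as for clinicians, if indicated, to account for the potential clustering effects of treatment within clinicians". Clinician is also absent from the examples of optional fixed covariates (demographics, primary diagnosis, number of visits). On the test itself: "The primary statistical test of interest will focus on the fixed effects term for treatment", at the 5% level.

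The reason offered for the clinician term is clustering, not the stratified design. Nothing else in the article commits the analysis to the randomisation strata, and Sample Size does not mention clinicians.

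**The concern.** Balancing the arms within each clinician removes between-clinician variation from the true sampling variance of the arm difference. A model with no clinician term does not know this. It leaves that variation in the residual, so its standard error is larger than the real one, and the precision bought by stratifying is not reported.

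The condition is also undefined. Read as analyst judgement, it makes the primary P value depend on a discretionary choice. Read as a significance test, it is a preliminary test that may have little power with a modest number of clinicians. At stake are some power and a clean, fixed primary model.

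**Working it through.** **Inputs from the article.** N = 100, taken as 50 per arm; at least 3 measures; d = 0.5; stated power 80%; significance at P<.05 (two-sided assumed); strata = treating clinician.

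**Assumptions, not in the article.** Within-patient correlation ρ; clinician share c of single-measure PHQ-9 variance; number of clinicians; a treatment effect common to all clinicians.

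**The plan's own figure.** In SD units, the mean of 3 measures has variance f = (1 + 2ρ)/3. Power = Φ(0.5/√(2f/50) − 1.96). This gives 86.5%, 83.1%, 80.1% and 76.6% at ρ = 0.5, 0.6, 0.69 and 0.8, and exactly 80% at ρ = 0.694. The stated 80% is attainable but cannot be confirmed, because ρ is not given.

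**If the clinician term is always omitted.** Take ρ = 0.6, so f = 2.2/3 = 0.733.
- Standard error reported by the model: √(2 × 0.733/50) = 0.171.
- True standard error with balance inside each clinician: √(2(f − c)/50).
- Type I error = 2[1 − Φ(1.96 × reported/true)].
- Power omitting = Φ((0.5 − 1.96 × 0.171)/true). Power including = Φ(0.5/true − 1.96).

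| c | True SE | Reported/true | Type I error | Power, omitted | Power, included |
|---|---|---|---|---|---|
| 5% | 0.165 | 1.036 | 4.2% | 84.0% | 85.6% |
| 10% | 0.159 | 1.076 | 3.5% | 84.9% | 88.1% |
| 20% | 0.146 | 1.173 | 2.2% | 87.0% | 92.8% |

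At ρ = 0.69 the picture is the same: type I error 4.3%, 3.6% and 2.3%; power 80.9% v 82.6%, 81.7% v 85.1%, and 83.6% v 90.1%.

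**If the term is kept only when tested significant.** The article states a conditional rule, so this case must be computed too. I simulated patient means (ρ = 0.6, 20,000 runs per setting), keeping clinician as a fixed effect when its F test gave P<.05.

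| Clinicians × patients | c | Term kept (null runs) | Type I, conditional | Power, conditional | Power, always in |
|---|---|---|---|---|---|
| 10 × 10 | 5% | 34% | 5.0% | 84.5% | 84.8% |
| 10 × 10 | 10% | 65% | 5.1% | 87.0% | 87.2% |
| 10 × 10 | 20% | 92% | 5.1% | 92.3% | 92.3% |
| 25 × 4 | 5% | 20% | 4.9% | 84.3% | 84.9% |
| 25 × 4 | 10% | 45% | 4.6% | 86.8% | 87.5% |
| 25 × 4 | 20% | 87% | 4.7% | 91.8% | 92.1% |
| 50 × 2 | 5% | 12% | 4.8% | 84.0% | 84.2% |
| 50 × 2 | 10% | 25% | 4.7% | 86.2% | 87.0% |
| 50 × 2 | 20% | 61% | 4.7% | 91.0% | 91.9% |

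With no clinician variance (c = 0), the conditional rule gave a type I error of 4.9% to 5.4%. Over repeated runs of these settings the range was about 4.4% to 5.4%. The largest power loss was about 1 point. The pretest is weak where the clinician share is small, but omission costs little there. Where the share is large, the term is usually kept.

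**The case against.** The strongest reply is that the article does name a clinician effect and says why, and that it is a condensed account. The criterion for including the term may sit in an analysis plan that is not shown. A test-based rule performs nearly as well as always including the term, and omission with a common effect is conservative. Most of this stands, and it is why the point is small. What remains is that the article is not silent on the matter: it states that the factor used to randomise is optional in the primary model, and it justifies the term by something other than the design.

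Two stronger readings are tempting, and neither is supported.
- **The type I error is not 5%.** This is clearly so only if the term is actually left out. Under a test-based rule it stays close to 5%.
- **Ignored clustering will produce false positives, or a biased estimate.** Randomisation is within clinician, so the estimate is unbiased, and with a common effect the error runs the other way. Inflation needs a treatment effect that differs between clinicians. Pragmatic Challenges concedes that clinicians may use the dashboard differently, but no size is given. As an illustration only: with ρ = 0.69, c = 5%, 10 clinicians and a slope variance of 0.10, the type I error would be about 7.5%; with a slope variance of 0.02 it would be about 4.9%. A clinician intercept would not cure such inflation.

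**Conclusion.** The point holds as a minor one. The design fixes treating clinician as the stratum, and the analysis leaves it to an unstated condition. The figures of 4.2%, 3.5% and 2.2% for type I error, and of 2, 3 and 6 points of power, are bounds for outright omission. They are not the expected effect of the plan as written. A test-based rule costs at most about 1 point of power.

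These sizes rest on assumed values for the clinician share, the within-patient correlation and the number of clinicians, and on a common treatment effect. The article gives none of them. The gain is a primary model that is fixed in advance and matches the randomisation.

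**What to change.** Delete the words 'if indicated'. State that treating clinician, as the randomisation stratum, is always in the primary and secondary models, whatever its estimated variance or test result. Use a random intercept with patients nested within clinician, or fixed effects if clinicians are few. A clinician-by-treatment random effect could be added as a sensitivity analysis, since use of the dashboard is expected to vary.

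The cost is wording only. Clinician defines the stratum, so it is known for every patient, and a random-effect variance estimated at zero does no harm. In the simulation with no clinician variance at all, always fitting fixed clinician effects changed power from 81.8% to 81.7% (10 × 10), 82.3% to 81.9% (25 × 4) and 82.1% to 81.4% (50 × 2), compared with omitting them. Data collection is complete but results are to be reported separately, so the model should be fixed before the arms are compared. If that is no longer possible, the clinician-adjusted model should be reported as the main analysis, with the timing of that decision stated.

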**Methods:**

We developed a personalized electronic dashboard that tracks patients’ electronic communications and social media activity, visualizes data on these interactions through key graphics and figures, and provides a tool that can be readily integrated into routine clinical care for use by clinicians and patients during treatment sessions. We then designed a randomized trial to evaluate the feasibility and effectiveness of using the electronic dashboard in real-world care compared to treatment as usual. The trial included patients aged ≥12 years with a mood or anxiety disorder who were receiving treatment in outpatient psychiatry clinics in the Johns Hopkins Health System and the Kennedy Krieger Institute. The primary outcome includes changes in patient-rated depression symptoms. Secondary outcomes include changes in patient-rated anxiety symptoms and overall functioning. Exploratory analyses examine the impact of the intervention on measures of therapeutic alliance and the detection of clinically actionable targets.

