#### Patient Measures

To measure proximal outcomes on mental health symptoms, participants completed the Patient Health Questionnaire-9 (PHQ-9) [58] and Generalized Anxiety Disorder-7 (GAD-7) [59] at the baseline and every subsequent clinic visit during follow-up. The PHQ-9 is a 9-item measure of current depressive symptoms ranging from 0 to 27, with higher scores representing greater levels of depression. The GAD-7 is a 7-item measure of current anxiety symptoms that ranges from 0 to 21, with higher scores representing greater levels of anxiety. In addition, to measure more distal outcomes on overall mental health–related quality of life, participants completed the Short Form-36 Health Survey Mental Health Component (SF-36 MHC) at baseline and every 3 months, coinciding with their nearest regularly scheduled clinic visit. This 13-item mental health component scoring ranges from 0 to 100, with higher scores indicating higher mental health–related quality of life [60]. We selected these measures as our primary (PHQ-9) and secondary (GAD-7 and SF-36 MHC) outcomes because they are brief, making them pragmatic to collect, and they are widely used with well-established psychometric properties for measuring important clinical outcomes that, based on the conceptual model we hypothesized, will improve with the proposed intervention.

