#### Data Management

The PHQ-9 and GAD-7 were collected as part of an MBC program that has been implemented in our clinics. As part of this program, patients completed the PHQ-9 and GAD-7 before every clinic visit through the Epic electronic health record as part of routine care. All other measures were collected remotely at the scheduled times via text with a link to questionnaire forms developed in a REDCap (Research Electronic Data Capture; Vanderbilt University) database that is maintained by approved study team members at Johns Hopkins University. These data are to be joined and processed for downstream analyses after removing all patient identifiers except for dates of service.

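### The primary test is a treatment main effect with no specified baseline PHQ-9 adjustment; if baseline is modelled as an outcome, as the wording suggests, the effect is diluted

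*Protocol article*

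**What the plan says.** The Statistical Analysis section describes one random effects linear model for PHQ-9, GAD-7 and SF-36 MHC, with fixed effects for arm and time and a random effect for patient. The primary test is the arm term: "The primary statistical test of interest will focus on the fixed effects term for treatment, which will provide an estimate of the mean differences". The section defends this choice on the ground that patients enter at any score: "we consider the model in which we control for time to be the most appropriate test of differences between the treatment arms". The interaction is optional: "we may consider examining interactions between treatment and time". The covariates given as examples are demographics, primary diagnosis and number of visits, all only to be considered. A baseline score is not among them.

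On what enters the model, the same section counts "the SF-36 MHC at baseline and end of the study, there are repeated measures over time for each scale within individual patients". Patient Measures says PHQ-9 and GAD-7 were completed "at the baseline and every subsequent clinic visit during follow-up". Data Management adds that "patients completed the PHQ-9 and GAD-7 before every clinic visit". Study Procedures defines the baseline visit: "The first regularly scheduled clinic visit with their clinician after the patient consented and downloaded the Bark app was considered" the baseline. The Abstract describes the endpoint as change: "The primary outcome includes changes in patient-rated depression symptoms".

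Sample Size claims 80% power for a Cohen d of at least 0.5 with 100 patients and at least three repeated measures.

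**The concern.** The baseline PHQ-9 is filled in before the first study visit, so no dashboard session can have influenced it and its expected arm difference is nil. If that score is one of the outcomes, a single arm term averages it with the follow-up differences and pulls the estimate toward zero. Whether or not it is an outcome, nothing in the text commits the primary analysis to adjusting for it. The reason offered for the model points the other way: admitting patients at any score implies a wide baseline spread, and that is when baseline adjustment gains most. At stake is a dashboard that works but is reported as having a smaller effect than it has, or none.

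**Working it through.** **Inputs from the protocol article.** 100 patients allocated 1:1, so 50 per arm; d = 0.5; at least three measures; P<.05 (Sample Size, Study Procedures, Statistical Analysis).

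**Assumptions.** Two-sided test; equal correlation r between any two scores of a patient, with r = 0.5, 0.6 or 0.7 because the article gives none; the same effect at every post-baseline visit; balanced visits; no dropout. Power is from the noncentral t with 98 degrees of freedom and noncentrality effect / sqrt(2f/50), where f is the variance factor of the patient-level summary.

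**The plan's own figure.** A single measure (f = 1) gives 69.7%. Three measures that all carry the full 0.5 have f = (1+2r)/3 and give 85.8%, 82.4% and 79.0% at the three correlations. So 80% can be matched with r a little under 0.7, but it cannot be strictly reproduced because r is not stated. With three measures in all, the match also requires each of them, including any baseline one, to carry the full effect.

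**Reading A: baseline is one of the outcomes.** With m post-baseline visits, effect = 0.5 × m/(m+1) and f = (1+mr)/(m+1).

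| Measures in all | Share of effect | Power, r = 0.5 | r = 0.6 | r = 0.7 |
|---|---|---|---|---|
| 3 | 2/3 = 67% | 52.4% | 48.7% | 45.4% |
| 7 | 6/7 = 86% | 80.1% | 74.5% | 69.2% |
| 13 | 12/13 = 92% | 87.6% | 82.0% | 76.6% |

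Example, three measures and r = 0.6: effect 0.333, f = 2.2/3 = 0.733, noncentrality 0.333/sqrt(2 × 0.733/50) = 1.95, power 48.7%. A check with 500 simulated mixed-model fits at r = 0.7 gave a mean arm estimate of 0.33 and power of 45%.

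**Reading B: only post-baseline scores are outcomes.** With k such scores, f = (1+(k-1)r)/k unadjusted. With baseline as covariate, r² is subtracted.

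| Post-baseline measures | Model | r = 0.5 | r = 0.6 | r = 0.7 |
|---|---|---|---|---|
| 2 | unadjusted | 81.6% | 79.0% | 76.6% |
| 2 | baseline covariate | 93.8% | 96.2% | 98.5% |
| 3 | unadjusted | 85.8% | 82.4% | 79.0% |
| 3 | baseline covariate | 97.0% | 98.2% | 99.4% |

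In the simulation at r = 0.7, two post-baseline measures with the baseline covariate gave a mean estimate of 0.50 and power of 98.4%.

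**SF-36 MHC, measured at baseline and end as Statistical Analysis describes it.** With m = 1 the arm term estimates half the effect (0.25 if the true effect is 0.5), with power 29.8%, 28.3% and 26.9%. With baseline as covariate, power is 81.6%, 87.2% and 93.4%. Table 1 schedules this scale every three months. On that schedule, with two follow-up scores, the share would be two thirds.

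**The case against.** The strongest objection is that no sentence says baseline PHQ-9 is modelled as an outcome. Statistical Analysis defines the primary outcome by reference to the follow-up course, and Patient Measures distinguishes the baseline visit from later follow-up visits, so a post-baseline-only analysis is a possible reading. The best evidence against that reading concerns another scale: SF-36 MHC at baseline and end is called repeated measures, which requires counting baseline. Because one model serves all three scales, the inference to PHQ-9 is strong, but it is still an inference.

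Three further points stand:

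- The covariates are introduced as examples in a condensed article, so baseline adjustment is unspecified rather than ruled out. A reader might infer that the plan throws the baseline score away; on Reading A it stays in the model, only not as an adjuster.
- Three measures is a floor. PHQ-9 is taken at every visit for up to six months in patients receiving ongoing psychotherapy. A reader might take 45% to 52% as the trial's power, but the article gives no visit frequency, so that range is only the minimum-visit case.
- A reader might see a contradiction between change in the Abstract and mean level in the Methods. The Abstract is reasonably read as shorthand, so little rests on it.

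The objection does not dispose of the point. The article does more than omit detail: it selects a main-effect contrast, defends it, and makes the interaction optional. On either reading the primary analysis is not committed to using the baseline score efficiently.

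**Conclusion.** The point holds in conditional form. If baseline PHQ-9 is an outcome, which is the more natural reading, the arm term understates the follow-up effect by 1/(m+1): a third with three measures in all, 14% with seven and 8% with 13. Power at the planned effect then falls below the stated 80% in most of the scenarios shown. If baseline is not an outcome, the estimate is not diluted, and the cost is an efficiency loss of about 12 to 22 percentage points of power with two post-baseline measures.

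The sizes rest on the assumed correlations, a constant effect, balanced visits and no dropout. With uneven visits, baseline weighs more in patients with few visits, so the dilution has no single value. Nothing here suggests false positives: randomisation keeps the test valid under the null. Nor do the documents support saying that the trial has only even odds of detecting its planned effect.

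**What to change.** State whether the baseline score is an outcome, and replace the primary contrast with one of the following:

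- **Preferred:** keep baseline in the outcome vector, constrain the arms to a common baseline mean, and test the arm-by-post-baseline contrast averaged over follow-up. This also keeps patients who have no later visit.
- **Alternative:** model post-baseline PHQ-9 with arm, time and baseline PHQ-9 as fixed effects, and test the arm term. This drops patients with no follow-up visit, so the two options are not interchangeable when visits are irregular.

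Apply the same choice to GAD-7 and SF-36 MHC. Restate the power calculation with the contrast, the number of post-baseline measures and the correlation assumed, and align the Abstract wording.

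No new data are needed, since baseline scores are already collected. The cost is procedural. The Results section says data collection is complete, so the change should be dated and made before arm-level results are seen. If that is no longer possible, disclose it as a late change and report the analysis as published alongside it.
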